### Sample size

Sample size was calculated using G*Power software version 3.1.9.3 with a power of 0.80 and α = 0.05 (two-tailed). Based on the results from previous studies on CBT/DBT treatment for adults and adolescents with ADHD [15, 21] we expect a reduction on the ASRS-A of about seven points (range is 0–72). A greater reduction of ADHD symptoms in the SSTG of seven points (SD = 12) on the ASRS-A and a greater reduction of four points (SD = 7) on functional impairment as measured by the CSDS would result in an effect size of 0.57 and a sample size of approximately 50 participants per group. Based on pre- and post-treatment measurements using the SDQ from the pilot study, at least 17 adolescents are needed to obtain a reduction of symptoms and 69 adolescents for a reduction of self-rated impairments using the paired sample t-test. Based on these power calculations and what was deemed feasible in the clinical settings, a study population of ≥100 was targeted.

## Discussion

This study will be the first RCT examining the acceptability and efficacy of a SSTG based on DBT for adolescents with ADHD. Recruitment and treatment ended during 2018, the last post-treatment assessments are now being completed. Treatments based on DBT may be of value for adolescents given that the explicit focus on interpersonal relations and emotional dysregulation corresponds to issues of importance during this age [1, 3]. Moreover, the group setting per se may be of importance during this phase of life knowing that adolescence is a time when peers’ behaviour and reasoning have a strong impact on the individual [48]. Thus, the group setting may further reinforce the learning process.

Our study has some limitations. First, the outcome measures are based solely on parental reports and self-reports of the adolescents, which may be subject to reporting bias. Indeed, although rating scales can reliably, validly and efficiently measure DSM-based ADHD symptoms in youths [49], to add a more objective outcome measure, such as assessment by an independent clinician, would have been preferable. Second, a rather large number of the participants (*n* = 32) did not start treatment after being randomised to one of the treatment arms. This pre-treatment drop-out rate may reflect aspects such as not being assigned to the desired treatment or a lack of motivation to participate in the treatment. Given consent to participate may reflect more of an impulsive decision or a willingness to please their parents or the clinician. An attrition analysis will be conducted to further assess potential reasons for attrition and differences between completers and non-completers on the study measures. Third, although we have an active control group, the length of the treatments differs between the two treatment groups, which may have an impact on the outcome measures. More treatment sessions may have a two-fold effect: more attention from the therapist and more time together with the other participants. However, it is not evident that a longer treatment would be perceived as more positive for this group of patients in that participating in a longer treatment is a more time-consuming process. Fourth, some minor adaptations of the treatment manual for the SSTG were conducted after the first round of treatment. However, a comparison between those who received the treatment pre- and post-final adaptations will be calculated for the outcome measures.

The study has some strengths, including being an RCT with an active control setting based on psychoeducation, the recommended first-line treatment. Moreover, data are collected from two information sources, offering the therapists training and supervision and checking adherence to the method. In addition, this study will be carried out at several locations in Sweden, making the sample potentially more representative of the target population. We believe that the study will extend the current knowledge base about psychological treatment for adolescents with ADHD.

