### Participants and procedures

Recruitment, treatment and data collection are conducted in seven cities in Sweden (Gävle, Falun, Karlstad, Uppsala, Uddevalla, Västerås and Växjö Additional file 1), beginning in 2015, with the last post-treatment measurement expected to be finalised in the spring of 2019. Adolescents (15–18 years of age) from the local child and adolescent psychiatric (CAP) outpatient units with a known diagnosis of ADHD have been informed about the study through flyers in waiting rooms, verbally by the clinical staff, or both. For those who have shown interest, more information has been provided at an extra meeting and the staff have evaluated the patients’ eligibility for the study (see below). Before final inclusion, participants and their parents provided written informed consent. Study participation is voluntary and can be interrupted by the participant at any time. Eligible patients have then been randomised to one of the two treatment conditions. Adolescent self-reports and parental ratings have been collected 2 weeks before the start of the treatment, during the treatment, and are continuously collected 2 weeks and 6 months after conclusion of the treatment. Pre- and post-treatment instruments are administered using an online platform to which only the research group has access and coded data is stored in a secure server. The participating parents are continuously reminded by the research team to complete the questionnaires. When both the adolescent and their parent have completed the last measurement, they will receive two cinema tickets. Initially, the plan was to continue the recruitment until at least 100 patients had completed treatment. In total, 184 patients have been randomised. Of these, 159 adolescents and 162 parents have completed baseline assessments and the last post-treatment evaluations are now continuously being collected (Fig. 1). Those who were randomised but never underwent a baseline assessment were considered external dropouts. Those who completed the baseline assessment, but did not complete the treatment, will be considered internal dropouts.

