### Randomisation

When eligibility assessment was completed, participants were randomised to one of the two study arms using a computer-generated allocation sequence (https://www.randomizer.org) with separate sequence lists for each treatment centre. The participants were randomly assigned in a 1:1 ratio. Codes were used to ensure information confidentiality and participant anonymity. Moreover, the principal investigator, who had no access to the identity of the participants, performed the treatment allocation based on the codes. Participants were not blinded to the treatment condition.

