A clinical child and adolescent psychologist, trained in both CBT and DBT, adjusted the manual for adolescents based on her clinical experience as well as from the results of the pilot study. The publisher gave us permission to continue to improve the manual for the age group. Further adaptations were discussed and revised in a reference group consisting of five psychologists and one social worker (two were trained DBT therapists and four CBT therapists), all working clinically in child and adolescent psychiatry. The following adaptations were implemented: The language was simplified and examples were adapted to the current age group; some theoretical sections were shortened and clarified; more practical exercises were included; and more examples of tools and skills were presented. Moreover, the number of homework assignments was decreased and no additional literature was recommended. One session was moved to an earlier stage in the programme (the session about emotions was now presented before the session about behavioural analysis) and the time spent on relational skills was increased with additional theory and practice. To make this feasible within the time frame of 14 sessions, the sessions about impulsivity and addiction were merged into one session. Major adaptations were done before the study start and some minor additions were introduced after the first round of treatment to further simplify and clarify the material. After the adaptations were consummated, the study supervisor reviewed the manual to ensure that the original method was preserved. All essential elements were kept.

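### The planned before-after check on the revised SSTG manual compares cohorts that were not randomised to a version; an ancillary arm-by-round estimate using the concurrent controls would answer the question better

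*Protocol article*

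**What the plan says.** The section on the SSTG arm in the protocol article reports that the main adaptations were made before the study began and that "some minor additions were introduced after the first round of treatment to further simplify and clarify the material". It adds that the study supervisor then reviewed the manual and that no essential element was lost.

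The Discussion lists the change as the fourth limitation: "some minor adaptations of the treatment manual for the SSTG were conducted after the first round of treatment". Its answer is that "a comparison between those who received the treatment pre- and post-final adaptations will be calculated for the outcome measures".

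On allocation, the Randomisation section states: "The participants were randomly assigned in a 1:1 ratio", "with separate sequence lists for each treatment centre". Data collection is described as "beginning in 2015, with the last post-treatment measurement expected to be finalised in the spring of 2019", and the Discussion states that "Recruitment and treatment ended during 2018".

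The Statistical analysis plan section specifies repeated-measures general linear models with the baseline value as covariate. It names no term for period or manual version. Its examples of subgroups are ADHD subtype and other psychopathology.

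**The concern.** The manual version a participant received depended on when that participant was treated. Early and late SSTG participants may also differ in who was referred first, in the mix of centres, and in how practised the therapists were. The planned contrast mixes all of this with the effect of the revision. A difference could arise without any manual effect, and a real one could be masked.

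The contrast also answers a different question from the one that matters for pooling. What matters is whether the SSTG-minus-control effect was the same under both versions. A change in outcome level among SSTG participants does not show that. Allocation was 1:1 with a separate list for each centre, so controls were randomised alongside SSTG participants and can supply the missing comparison. The article's own Background draws the lesson from the adult SSTG literature that uncontrolled results need a randomised comparison.

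**Working it through.** **1. The plan's own figures.** The article states no figure for this comparison. The nearest is the main sample size: effect size 0.57, power 0.80, two-sided α 0.05. Normal approximation: n per group = 2(1.960 + 0.842)²/0.57² = 15.70/0.325 = 48.3, so 49. The t-test version gives 49.3, so 50. The stated figure of about 50 per group reproduces. The planning SD of 12 on the ASRS-A from the same section is used below.

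**2. What each contrast estimates.** Let M be the manual effect, D the drift common to both arms, and T any change over time specific to SSTG delivery, such as growing therapist experience.

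- Within SSTG, late minus early: M + D + T.
- Within control, late minus early: D.
- Arm-by-round interaction, the first minus the second: M + T.

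The planned contrast carries D in full. The interaction removes D in expectation but not T.

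**3. Precision.** Assumptions: 159 adolescents analysed, so about 80 per arm; SD 12; the same early/late split in both arms, with 15 to 30 of 80 in round one.

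- SE within SSTG = 12 × √(1/n_early + 1/n_late)
- SE of interaction = √2 × SE within SSTG
- Chance of nominal significance with no manual effect = Φ(D/SE − 1.96) + Φ(−D/SE − 1.96), taking T = 0
- Difference detectable with 80% power = 2.802 × SE

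| Early/late per arm | SE within | SE interaction | False signal, planned contrast, D = 2 | Same, D = 4 | Detectable, within | Detectable, interaction |
|---|---|---|---|---|---|---|
| 15/65 | 3.44 | 4.86 | 0.09 | 0.21 | 9.6 | 13.6 |
| 20/60 | 3.10 | 4.38 | 0.10 | 0.25 | 8.7 | 12.3 |
| 30/50 | 2.77 | 3.92 | 0.11 | 0.30 | 7.8 | 11.0 |

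The drift values of 2 and 4 points are illustrative. With the early share varied from 15% to 50%, a drift of 3.5 points (half the planned 7-point effect) gives a false-signal rate of about 0.15 to 0.26.

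**4. Bias against precision.** Root mean square error of the planned contrast is √(SE² + D²). At D = 2 it is √(3.44² + 2²) = 4.0 down to √(2.77² + 2²) = 3.4, against 4.9 down to 3.9 for the interaction. The two are equal when D equals the within-SSTG SE, that is, at 2.8 to 3.4 points.

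**5. Sensitivity run without round one.** SE of the arm difference = 12 × √(2/n per arm). With 80 it is 1.90, with 65 it is 2.10, and with 50 it is 2.40. Little precision is lost.

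**The case against.** The strongest reply is that this is a single sentence among the limitations in a condensed article, about changes described as minor. It fixes no test, decision rule or interpretation, and the model for an ancillary check is normally left to an analysis plan that is not shown. If the baseline-adjusted model is used here, part of any difference in baseline severity between early and late referrals is removed. The remedy also has limits of its own. It leaves SSTG-therapist experience mixed with manual version, it has the smaller mean square error only when shared drift exceeds about 2.8 to 3.4 points, and a change of 7 points would be found with power of only about 0.30 to 0.43. All of that stands. It keeps the severity low and means the result should be read as an estimate, not as a test. It does not repair the stated contrast, whose groups are named and exclude the controls on the natural reading.

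Stronger readings are tempting and are not supported:

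- A reader might infer that drift will be mistaken for a manual effect. The article gives no evidence that drift occurred and does not say how the result will be interpreted. The supportable statement is that the two cannot be separated.
- A reader might infer that use of the controls is ruled out. They are not mentioned for this question, which is not the same.
- A reader might infer that the comparison is the only support for pooling the two versions. The supervisor's review of the manual is also offered, although it concerns content and is not an analysis of outcomes.

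**Conclusion.** The point holds as an ancillary improvement of low severity. The stated check is a non-randomised before-after contrast. It cannot separate manual version from cohort or period differences, and it does not address whether the randomised effect changed. Using concurrent controls removes drift shared by the arms, at a standard error of about 3.9 to 4.9 instead of 2.8 to 3.4 ASRS-A points. Those figures rest on SD 12, about 80 per arm and 15 to 30 per arm in round one. The article does not give the split, and it reports nothing about drift.

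A reader might go on to infer that the main result is compromised. It is not: SSTG and control were randomised against each other throughout, and the primary contrast averages over both manual versions without bias from this check.

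**What to change.** Leave the primary model unchanged; an interaction term there would make the arm coefficient depend on how round is coded. In a separate ancillary model, estimate the arm-by-round interaction, first round versus later rounds. Define round for both arms within centre, from the time of randomisation, and adjust for baseline and centre. Report the estimate with its confidence interval, alongside or in place of the within-SSTG contrast. Add one sensitivity run of the primary contrast that excludes the first round in both arms.

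State three limits with the result:

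- The interaction removes only drift common to both arms.
- Growing experience of the SSTG therapists stays mixed with manual version.
- A non-significant interaction is not evidence that the revision had no effect.

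The cost is a change of wording and two model runs on data already collected. The article places the start of analysis in summer 2019, after its own writing, so the wording could be settled first. The downside is the wider interval.

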## Abbreviations

ADD: Attention deficit disorder
ADHD: Attention deficit/hyperactivity disorder
ASRS-A: Adult ADHD self-report scale for adolescents
BPD: Borderline personality disorder
CAP: Child and adolescent psychiatric
CBT: Cognitive behavioural therapy
CSDS: Child Sheehan disability scale
DBT: Dialectical behaviour therapy
DSM: Diagnostic and statistical manual of mental disorders
FFMQ: Five facet mindfulness questionnaire
GQL: Global quality of life
HAD: Hospital anxiety and depression scale
IAS: Impact of ADHD symptoms
KSQ: Karolinska sleep questionnaire
LMCF: Last mean carried forward
MINI-KID: Mini International Neuropsychiatric Interview for Children and Adolescents
PAS: Pressure activation stress scale
RCT: Randomised controlled trial
SDQ: Strength and difficulties questionnaire
SSTG: Structured skills training group
